#### Secondary aims

To investigate the relationship between specific genetic polymorphisms and the development of depression during pregnancy and the postpartum (substudy Life-ON 1)To investigate the effectiveness of BLT in treating PND (substudy Life-ON 2).To test whether a short term trial by BLT in non-depressed pregnant women can prevent the onset of PND (substudy Life-ON 3)

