Life-ON 1 substudy consists in a genetic test on a blood sample taken during the 23rd-25th gestational week, with the aim to identify possible specific genetic polymorphisms, that may be associated with PND. Part of the blood samples taken at inclusion will be processed and stored in a bio-bank for future use.

### Experimental design – substudy Life-ON 2

Life-ON 2 is a longitudinal and interventional trial, which will investigate the effectiveness of BLT in treating PND. Women with minor or major depression, diagnosed by a psychiatric interview or with an EPDS score >12 at any time from study inclusion to 9 months postpartum, will be invited to participate in the randomized-controlled BLT trial. Participants will be randomised on a 1:1 basis to receive 6 weeks of morning BLT or dim light placebo. The trial will be single blind. Subjects will be asked to maintain their habitual bedtime and wake-up schedule, and to begin the light treatment within 20 min of habitual wake-up time. Subjects will be instructed to sit in front of the light box (Philips Energy Up HF 3419) at a specified distance (around 30 cm) and to receive an active light dose (10’000 lux) or placebo dim light (50 lux) for ½ hour. Safety will be monitored with the self-report version of the Systematic Assessment of Treatment Emergent Effects (SAFTEE). Similarly to Life-ON, all participants will be followed up until 12 months postpartum.

### Experimental design – substudy Life-ON 3

Life-ON 3 is a longitudinal and interventional trial, in non-depressed women, which will investigate the effectiveness of BLT during pregnancy in preventing PND. A subsample of 80 subjects without depression will be randomly, consecutively recruited to receive 6-week open-label BLT during the third trimester of pregnancy. The selected participants will receive ½ hour of morning BLT (10’000 lux, Philips Energy Up HF 3419) for 6 weeks. Subjects will be asked to maintain their habitual bedtime and wake-up schedule, and BLT is planned to commence within 20 min of habitual wake-up time. Safety will be monitored with the Systematic Assessment of Treatment Emergent Effects (SAFTEE). All participants will be followed-up until 12 months postpartum and the main outcome will be the incidence of postpartum depression in subjects receiving BLT compared to subjects with no treatment.

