### Determination of sample size

This prospective, longitudinal cohort study will include 500 pregnant females. Given that we consecutively include participants, we judge this sample size as sufficient to generate estimates for the prevalence of perinatal depression, sleep disturbances, and sleep disorders during pregnancy and postpartum. Based on a meta-analysis of prevalence and incidence studies we expect the cumulative incidence of minor and major depression during late pregnancy and postpartum to be at least 20 % (*n* = 100). Taking into consideration that we plan to include 80 females in a trial of light treatment for the prevention of postpartum depression, we expect that approximately 300 females will be symptom free, while 100 to 150 females will experience minor or major depression during the perinatal period. For the study of risk factors involved into the development of perinatal depression, our sample size will enable the detection of small to moderate effects (d > 0.3) with an adequate statistical power (≥80 %).

For the Life-ON study no significance threshold a priori is considered.

The main outcomes of Life-ON 2 will be the change of depressive symptoms, response and remission rates after 6-week bright light treatment versus placebo. Based on a previous meta-analysis we expect that the prevalence of depression during the perinatal period will be at least 25 %, which would qualify 125 participants for inclusion in the treatment trial. From our previous experiences we anticipate an attrition rate of 25 % for reasons of refusal, non-compliance, or necessity for additional/alternative treatment. A conservative estimate would, therefore, be that 80 females will complete the treatment trial. At the same time, weekly monitoring is expected to increase compliance and reduce attrition and the available data suggests that prolongation of the treatment duration to 6 weeks will increase the bright light versus placebo difference. Our conservatively planned sample size (40 versus 40) will enable us to demonstrate medium effects (d >0.56) with a one-side error level of 0.05 and adequate statistical power (≥80 %).

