### Statistical analyses

Standard parametric or non-parametric statistical tests will be employed to explore differences between females with onset of depression to those remaining symptom free. To take full advantage of the longitudinal study design, generalized mixed modelling will be employed to test whether sleep-related and other fixed or variable markers can predict the onset of perinatal depression, possibly in a time-associated manner. The evaluation of BLT effectiveness for perinatal depression should take into account that this therapy will be applied at different times during the perinatal period; therefore, this will be included as a covariate in the ANCOVA (continuous data) and logistic regression analyses (dichotomous data, proportions). Regarding the efficacy of BLT in prevention of post-partum depression we will use logistic regression analysis to compare incidence rates between the group of not-depressed patients who received light therapy during pregnancy versus untreated subjects. For all analyses *p* values < 0.05 will be considered significant. The statistical analysis will be performed using a dedicated software (SPSS, IL, USA).

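### A flat 0.05 rule for all analyses conflicts with the no-threshold statement for Life-ON and, as written, reaches the Life-ON 1 polymorphism tests without allowance for several variants

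*Protocol article*

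**What the plan says.** Four places in the protocol article bear on this.

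- **Statistical analyses.** The section lists comparisons of depressed with symptom-free women, mixed models that test whether "sleep-related and other fixed or variable markers can predict the onset of perinatal depression", and the analyses of the two light-therapy substudies. It then states, for all analyses, that p "values < 0.05 will be considered significant". It mentions no adjustment for several tests.
- **Determination of sample size.** "For the Life-ON study no significance threshold a priori is considered".
- **Secondary aims.** The first is "To investigate the relationship between specific genetic polymorphisms and the development of depression during pregnancy and the postpartum", labelled as substudy Life-ON 1.
- **Experimental design – substudy Life-ON 1.** A blood sample is tested "with the aim to identify possible specific genetic polymorphisms, that may be associated with PND".

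The number of polymorphisms is given nowhere. The article uses the name Life-ON study for the main observational cohort and lists the genetic work separately as a substudy. Women are asked to join that substudy additionally and voluntarily, with its own consent (Description of the study).

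**The concern.** There are two linked problems.

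First, the sample-size section sets no threshold for the main Life-ON analyses, while the analysis section calls anything below 0.05 significant in every analysis. An analyst cannot follow both.

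Second, the exemption names only the Life-ON study. On the article's own usage that is the main cohort, so Life-ON 1 stays under the flat rule. A search over several variants is where a per-test 0.05 does most harm, because each further variant with no real effect adds another chance of a spurious finding.

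At stake is what can be said under the first secondary aim. A polymorphism reported as significant could be the product of the number of variants examined, and the published rule would give the reader no protection against that.

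**Working it through.** **No plan figure to reproduce.** The article gives no variant count, error rate, sample size or power for Life-ON 1.

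**The statements side by side.**

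| Analyses | Sample-size section | Statistical analyses section |
|---|---|---|
| Main Life-ON markers | no threshold in advance | p < 0.05 significant |
| Life-ON 1 polymorphisms | not mentioned | p < 0.05 significant, through the all-analyses wording only |

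The first row is a contradiction. In the second row the universal wording is the only rule that applies, unless the exemption is read as extending to the substudy.

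**Inputs.** Per-test level 0.05 (Statistical analyses). Number of variants m: not in the article, so a range is assumed. Assumed throughout: no variant is truly associated with perinatal depression, and the tests are independent.

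**Formulas.** Chance of at least one false positive = 1 − 0.95^m. Expected number of false positives = 0.05 × m.

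| m | 1 − 0.95^m | 0.05 × m |
|---|---|---|
| 5 | 22.6% | 0.25 |
| 10 | 40.1% | 0.50 |
| 13 | 48.7% | 0.65 |
| 14 | 51.2% | 0.70 |
| 20 | 64.2% | 1.00 |
| 50 | 92.3% | 2.50 |

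The chance passes one half when m > ln(0.5)/ln(0.95) = 13.5, so from 14 independent tests.

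**Correlation.** Variants may be correlated. Simulating 20 two-sided tests with a common correlation of their test statistics gave 62.6% at correlation 0.1, 54.1% at 0.3, 42.0% at 0.5 and 28.9% at 0.7. The inflation shrinks but stays well above 5%.

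**With an adjustment.** For an assumed 20 independent variants, Bonferroni uses 0.05/20 = 0.0025 per test, and the chance of any false positive is 1 − 0.9975^20 = 4.9%. When no variant is associated, every rejection is false, so a 5% false-discovery rate also holds that chance at 5% for independent tests. When some variants are associated, it is less strict than Bonferroni.

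**Power cost, as an illustration only.** Suppose that every cohort member joins Life-ON 1, giving 100 cases and 300 symptom-free women (the planning section expects "approximately 300 females will be symptom free, while 100 to 150 females will experience minor or major depression"). Assume an allele frequency of 0.3 among the symptom-free and a two-sided allelic test on 200 against 600 alleles. Moving from 0.05 to 0.0025 lowers power from 98.4% to 86.8% at an odds ratio of 2.0, and from 87.8% to 55.4% at 1.7. Uptake, allele frequency, odds ratios and the 20 variants are all assumptions. A false-discovery-rate rule costs no more than Bonferroni.

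**The case against.** The strongest reply is that the article describes no genetic analysis. The section that carries the 0.05 rule never names polymorphisms; the nearest wording is about other fixed markers. A condensed article may leave the genetic methods to the full protocol or analysis plan, and a level of 0.05 is also what one would apply to adjusted p values. The genetic aim is worded tentatively, as a search for possible polymorphisms that may be associated, and Life-ON 1 is secondary and voluntary.

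Much of this stands. The absence of a named multiplicity method is not the point here, and the aim promises no confirmatory gene claim. What remains is that the article states a rule and gives it universal scope. An analysis plan that kept to the sample-size statement for the main cohort would depart from that rule. One that adjusted the genetic tests could be squared with it only by reading the p values as adjusted ones, which the article does not say. If a reader holds that the no-threshold statement covers Life-ON 1 too, the two sections then contradict each other on the genetic tests as well, and still need reconciling.

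A reader might infer that a false gene finding is more likely than not. The article does not support that: it gives no variant count, the statement needs at least 14 independent tests with no true association, and the word specific fits a short candidate list. Nor can one say that the trial will report chance findings as established, or that about 100 genetic cases will be available. The 100 to 150 refers to the whole cohort, and fewer may consent to the genetic test.

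**Conclusion.** The concern holds in a limited form. The two sections contradict each other on whether 0.05 applies to the main Life-ON marker analyses, and as written the flat rule reaches Life-ON 1 with no allowance for testing several variants. Its size depends on a variant count that the article does not give. Even a list of 5 carries more than four times the nominal 5% (22.6/5 = 4.5), if the tests are independent and no variant is associated; correlation would lower this. Because Life-ON 1 is an exploratory secondary substudy, the light-therapy comparisons do not depend on this point. It should still be corrected before any genetic result is described as significant.

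**What to change.** Reword the closing threshold sentence of Statistical analyses so that it no longer covers all analyses and agrees with Determination of sample size:

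- **Main Life-ON marker analyses:** exploratory, reported with estimates and confidence intervals, with no claim of significance.
- **Life-ON 1:** list the polymorphisms before analysis and treat them as one family. Declare a variant associated only at a Benjamini-Hochberg false-discovery rate of 5%, and label unadjusted p values exploratory.
- **Life-ON 2 and Life-ON 3:** state their thresholds separately. The rewording should not simply grant Life-ON 2 a flat 0.05 on each outcome, since the sample-size section names three main outcomes for it (symptom change, response and remission).

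This takes a few sentences and changes neither recruitment nor data collection. The cost is fewer nominal genetic findings and lower power for small genetic effects. How much lower depends on uptake of Life-ON 1, the variant count and the allele frequencies, none of which the article gives.

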## Discussion

The presented project aims to address several questions concerning PND, including epidemiology, pathophysiology, prevention and treatment. It may substantially contribute to a better knowledge of the relationship between sleep disorders and PND, as well as of the feasibility, safety and efficacy of BLT both in prevention and treatment of depression during pregnancy and the postpartum period. The characterization of specific risk factors for PND will critically contribute to the development of preventive medical and social strategies for the affected women and alert the healthcare community to this relevant and frequent mental health problem. Finally, we expect that our research will significantly contribute to improve care and treatment for women during and after pregnancy and ultimately to the long-term wellbeing of mothers, children and their families.

## Abbreviations

BLT: Bright light therapy
CRF: Case report form
ECG: Electrocardiogram
EEG: Electroencephalography
EMG: Electromyography
EOG: Electrooculography
EPDS: Edinburgh perinatal depression scale
ESS: Epworth sleepiness scale
GCP: Good clinical practice
HDRS-21: Hamilton depression rating scale – 21 items
IRLE: Interview for recent life events
ISI: Insomnia severity index
MADRS: Montgomery-Asberg depression rating scale
MDD: Major depression disorder
MEQ: Morningness-eveningness questionnaire
MINI-Plus: MINI international neuropsychiatric interview - plus
MINI: MINI international neuropsychiatric interview
MUPS: Munich parasomnia screening
PLM: Periodic leg movements
PND: Perinatal depression
PSG: Polisomnography
PSQI: Pittsburgh sleep quality index
RLS: Retless legs syndrome
SAFTEE: Systematic assessment of treatment emergent effects
SWS: Slow wave sleep
TCI: Temperament and character inventory
VAS: Visual analogic scale
